### Project 2 – Mātauranga Tuku Iho (intergenerational knowledge and language in action)

This project will highlight the role of kaumātua as carriers of mātauranga [21]; specifically, utilising cultural knowledge exchange as a driver for physical activity. The innovation of this project is that it provides an avenue to increased intergenerational exchange and physical activity that is consistent with cultural values and community activities. The pursuit of cultural knowledge for perpetuating/improving subsequent generations is a key theme of cultural narratives [126], such as Tāne’s ascension and descension through the 12 heavens to obtain the baskets of knowledge [127]; and then to share that knowledge for the preservation and perpetuation of whakapapa (genealogy). Māori narratives centre on “ako” where a reciprocal relationship of mutual learning and teaching between kaumātua and whānau (especially mokopuna or grandchildren) leads to “māramatanga” (change and insights) [128].

A key element of mātauranga is te reo Māori and the project will include language lessons for kaumātua who are not fluent speakers. This is especially important in the context of a generation of kaumātua who faced assimilation policies and practices and were discouraged from learning te reo and hence have experienced cultural dissonance. Research shows a link between speaking te reo, and cultural continuity, which have positive health outcomes [51, 129] including a positive association with HRQOL [40]. This approach involves teaching te reo Māori within the context of learning and sharing mātauranga such as mihi, whakapapa (genealogy), karakia (prayer), and waiata (songs).

The expectation is that the project will be divided into a series of wānanga (or group meetings) that provide instructional sessions about language, tikanga and physical activities across a range of skill levels. The sessions will be tailored to the needs of kaumātua given their previous experiences and knowledge about the session content. The content of the wānanga will be developed through a co-design process with providers and kaumātua and will be documented upon completion.

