After the wānanga kaumātua will be asked to engage with at least one member of their whānau to share mātauranga and speak/share reo while participating in a regular activity (e.g., walk to a sacred place; its importance and imperative to preserve the mātauranga of these sacred places is to pass this knowledge on and share stories/pūrākau) that helps improve physical functioning (e.g., participating in Kaumātua Olympics [fun, semi-competitive activities], Iron Kaumātua [triathalon], or simply starting to walk regularly). The intervention is designed to create individually determined improvements on the targeted outcomes. Figure 3 displays a flow diagram of proposed recruitment and data collection procedures.

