**Fig. 3 Fig3:**
[figure not shown]
Planned CONSORT Flow Diagram and Data Collection for Project for Mātauranga Tuku Iho. Note: Participants not allocated to intervention, lost to follow up and excluded from analysis will be calculated at the conclusion of the intervention

The specific measures likely will include quality of intergenerational relationships [130], cultural knowledge [102], cultural identity [40], resilience [131], physical functioning [132, 133], and te reo ability. This project will be registered with the Australia New Zealand Clinical Trial Registry, along with completing the application for research ethics after the co-design phase. The project starts 6 months post the start of the tuakana-teina project (originally was 1 year, but COVID-19 restrictions postponed the start of tuakana-teina).

The sample size of 90 kaumātua and 90 whānau members across six providers (*n* = 15 pairs each) was determined by a balance of resources and power to determine the optimal design and confirmed with NCSS-PASS software [134]. Sixty participant dyads are expected to be retained given the 67% retention rate in our previous research [36]. This sample size is sufficient to detect a small to medium effect size (d = .2, power = .80, *p* = .05) in time from pre-test to final post-test and a small to medium effect (d = .3, power = .80, p = .05) for group X time interaction. The chosen effect size is based on a recent study about the impact of small amounts of physical activity on physical functioning for older people [135]. A similar effect is expected for the other specific variables, particularly cultural knowledge for whānau.

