To test the objective, a mixed model analysis will be used where the participant responses over time are nested within individuals and nested within providers (i.e., three-level model). Mean responses for each of the key outcomes will be used as the dependent variables (e.g., HRQOL, life satisfaction, physical functioning, cultural knowledge exchange). The model will include the following independent variables: a) within group responses (i.e., responses for three time periods) for change over time; b) intervention received or not to identify intervention effect; and c) random intercepts to account for different teina baseline scores. Co-variates will include any independent variables that differ between the two approach groups at the baseline period. An intent-to-treat analysis will be used for the primary testing. A dose-response model will be considered including the number of interactions between kaumātua and whānau members, the amount of activity engaged in, and measures of the paired relationship of kaumātua and whānau member (e.g., degree of agreement in cultural exchange). It will be determined whether missing data due to loss to follow up can be multiply imputed via chained equations [125].

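### Project 2's optional dose-response model counts paired-relationship measures as dose although they overlap with two planned outcomes, so for those outcomes a positive slope can arise with no effect of the approach

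*Protocol article*

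**What the plan says.** All references are to the protocol article, section Project 2 – Mātauranga Tuku Iho.

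- **Dose terms** (last paragraph of the section). "A dose-response model will be considered including the number of interactions between kaumātua and whānau members", followed by "the amount of activity engaged in, and measures of the paired relationship of kaumātua and whānau member (e.g., degree of agreement in cultural exchange"). So there are three kinds of term: a contact count, an amount of activity, and measures describing the pair.
- **Outcomes** (same paragraph). Mean responses for the "key outcomes will be used as the dependent variables (e.g., HRQOL, life satisfaction, physical functioning, cultural knowledge exchange").
- **Project-specific measures** (paragraph after Fig. 3). "The specific measures likely will include quality of intergenerational relationships", with cultural knowledge, cultural identity, resilience, physical functioning and te reo ability after it. The list is provisional.
- **Place of activity.** The section describes the project as "utilising cultural knowledge exchange as a driver for physical activity". Kaumātua are asked to share knowledge with whānau "while participating in a regular activity" that is meant to help physical functioning.
- **Primary test.** Intent-to-treat. The dose-response model is something to be considered in addition.

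**The concern.** A dose-response slope is informative only if the dose is something received, measured separately from the result. A score for how well a pair relate, or how far they agree about their cultural exchange, describes the state of the pair after the approach has begun. Two of the planned outcomes describe much the same state. Pairs who are close, or who answer in a similar style, will tend to score high on both whether or not the approach did anything.

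The risk is that such a slope is presented as support for the approach when it reflects shared content and shared timing of measurement. Because the article names these terms itself, an analyst following it would fit this model.

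**Working it through.** **1. Dose terms set against outcomes**

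| Dose term | Planned outcome with the same content? | Nature of the problem |
|---|---|---|
| Number of interactions | None | An ordinary exposure count |
| Amount of activity | Not a listed outcome; physical functioning is | Post-baseline adherence, open to confounding by baseline functioning |
| Paired-relationship measures, e.g. agreement over cultural exchange | Cultural knowledge exchange; quality of intergenerational relationships | Overlap in construct |

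Only the third row sets related constructs on both sides of the model.

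**2. How large a spurious slope could be**

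The article states no figure for this model, so there is nothing to reproduce. Its sample size gives n: 90 kaumātua × 0.67 retention = 60.3, in line with the 60 dyads stated.

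Assumptions, none of them from the article: no effect of the approach; standardised scores; correlation ρ = .6 between pre-test and post-test outcome; dose correlated r with the post-test outcome through shared content only; two-sided 5% test; 60 independent people, ignoring provider clustering. The post-test outcome is regressed on the pre-test outcome and the dose.

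- Expected slope on dose = r(1 − ρ²) / (1 − r²ρ²)
- Partial correlation = r√(1 − ρ²) / √(1 − r²ρ²)
- Rejection probability ≈ Φ(atanh(partial correlation) × √(n − 4) − 1.96)

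At r = .3: slope = .3 × .64 / (1 − .09 × .36) = .192 / .9676 = .198. Partial correlation = .24 / .984 = .244. Then atanh(.244) × √56 = .249 × 7.48 = 1.86, and Φ(1.86 − 1.96) = Φ(−.10) = .46.

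Simulation with 4,000 runs per setting agrees:

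| r | Mean slope | Slope significant, no true effect |
|---|---|---|
| 0 | .00 | 4.9% |
| .2 | .13 | 24% |
| .3 | .20 | 47% |
| .5 | .35 | 92% |
| .7 | .54 | 100% |

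These results already include adjustment for the pre-test value. A random intercept does not help either: it absorbs stable differences between people, whereas this overlap is in the state at follow-up.

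**3. Amount of activity**

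Here the plausible mechanism is that fitter kaumātua do more. If activity depends only on baseline functioning, it is independent of follow-up functioning once baseline is held fixed, so a test adjusted for baseline keeps its 5% level. A simulation of that case used n = 60, no effect and 300 runs per setting. The pairs are the activity–baseline correlation and the stability of functioning.

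| Analysis | .3 / .7 | .4 / .8 | .5 / .9 |
|---|---|---|---|
| Raw correlation, positive and significant | 40% | 72% | 96% |
| Adjusted for pre-test value, either direction | 3% | 7% | 7% |
| Random-intercept model over three waves, positive and significant | 2% | 5% | 4% |

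The inflation belongs to the raw correlation and disappears under adjustment.

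**The case against.** The other side has several good points.

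- **The model is optional and secondary.** It will only be considered, and nothing in the article says it would carry the conclusion. This stands, and limits the weight of the point.
- **Agreement is not level.** Concordance within a pair is related to the amount of exchange or the quality of the relationship but is not the same, and the measures are only likely ones. This stands as a reason to say the constructs overlap rather than coincide. It does not remove the problem, because agreement is given as one example of a broader class of relationship measures.
- **The overlap touches two outcomes.** HRQOL, life satisfaction and physical functioning do not share this content. This stands.

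Three stronger readings are tempting, and the article does not support them.

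- *All the dose terms apart from contacts are outcomes.* A reader might infer this for activity from the statement that knowledge exchange drives it. But activity is not listed as an outcome, and the approach asks participants to do it.
- *Activity gives a built-in slope for physical functioning.* Large false-positive rates follow only from a raw correlation. The planned analysis uses repeated measures with random intercepts. A residual risk remains if activity tracks concurrent rather than baseline functioning, and the article does not say how dose would be coded.
- *The contact coefficient is distorted by adjusting for its own consequences.* This requires all terms to enter together, which the article does not say.

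**Conclusion.** The point holds for one term. Paired-relationship measures should not serve as dose for cultural knowledge exchange or for the quality of intergenerational relationships, because a positive slope can appear there without any effect and baseline adjustment does not prevent it. At 60 kaumātua even a modest shared correlation of .2 to .3 would raise a nominal 5% test to about 24% to 47%. Those percentages rest on the assumed .6 between waves and the assumed r, and show scale only. The conclusion itself rests on the overlap of constructs and on both being measured after baseline.

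Amount of activity is a usable adherence measure that needs care over confounding. The intent-to-treat test, the sample size and the power statement do not depend on this model.

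**What to change.** In the Project 2 analysis paragraph:

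1. Remove the paired-relationship and agreement measures from the dose terms. Analyse them as outcomes of allocated group, or as mediators.
2. Define dose by the number of kaumātua–whānau interactions. Keep amount of activity as a separate adherence measure.
3. Adjust the dose model for the pre-test value of the outcome, and for baseline physical functioning where activity is the dose.
4. Label the result an exploratory association that is not evidence of effect.

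The cost is wording; the contact count and the amount of activity are already among the planned terms, and physical functioning is among the likely measures. The price is a more modest dose-response claim.

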## Discussion

Epistemologically, kaumātua mana motuhake highlights the strengths and mana (status) of being a kaumātua [136]. It is almost redundant to outline from a customary and philosophical standpoint that Māori culture venerates its elders, such is its centrality to a Māori way of life; from the way that many Māori whānau operate beyond the bounds of a typical nuclear family, to tikanga (cultural practices) observed on marae (community meeting place) and in various community settings. As Sir Hirini Moko Mead states: “[t] he kaumātua and kuia, the elders, are often the guardians of tikanga. They are expected to know” and “[e] xperience is definitely helpful in knowing what to do (p. 14).” [137] Also, as Sir Mason Durie puts it: “[w] hen other New Zealanders might be contemplating withdrawal from public life, older Māori are often encouraged to accept new responsibilities expected by their own people – self-interest will give way to the interests of whānau and hapū (p. 4)” [138].

KMMP takes a strengths-based approach that conceptually reframes the notion of ageing away from a deficit model [139], discourse, which assumes an increasing percentage of older people over the first half of the twenty-first century is coterminous with an increasing burden on the socio-economic system; a discourse underpinned by a deficit model that focuses on isolation, vulnerability, limitations and dependency [136, 140]. The central discourse needs to shift if Aotearoa is to re-comprehend older people as highly valuable members of society. The esteem of elders in Māori culture in principle (if not always in practice) signals transformative potential.

Similarly, one of the issues with the majority of current health research and Indigenous peoples is that it is often validated via a logic of disparity, where Indigenous health statistics are measured against a non-Indigenous baseline. Whilst the logic of disparity helps to define the problem, in doing so it simultaneously defines Indigenous peoples as ‘the problem’ to be fixed and, consequently, falls into the trap of a deficit model framing [141]. In contrast, this research acknowledges that the problem is not kaumātua, rather the comparatively poor Indigenous health statistics are directly related to colonisation and the continued structural discrimination within the health system itself. Although health research in this space is in its infancy, the broader thesis to be tested is that Indigenous cultural revitalisation will increase the wellbeing of Indigenous communities. The cultural dissonance and, therefore, the cultural continuity of Indigenous peoples is an under-investigated concept in health literature, especially in relation to the elderly. This research directly investigates this concept by examining the association between kaumātua culture and health in relation to learning te reo Māori; mātauranga; and tuakana/teina.

The present research, therefore, is original and innovative, and will methodologically contribute to research being carried out in other settler-colonial contexts. Two specific outcomes are anticipated from this research; firstly, it is hoped that the research methodology provides a framework for how government agencies, researchers and relevant sector stakeholders could work with Māori communities. This project will help demonstrate that a participatory approach following the He Pikinga Wairora framework [88] working with end-users, using systems thinking and centring on kaupapa Māori provides a strong approach leading to positive health outcomes and health equity. Secondly, the two individual projects will each produce a tangible approach that, it is anticipated, will be cost effective in enhancing kaumātua hauora and mana motuhake. These products will be made accessible to various end-users and, if effective, will enable advocacy with stakeholders and policy-makers to include them as part of the means to serve the rapidly growing population of kaumātua. The point of the research is, therefore, not to simply accept that the tikanga surrounding Māori elders trickles down to all Māori and indeed to the ageing population in Aotearoa as a whole, but rather to employ cultural concepts to help shift the public discourse surrounding ageing and to contribute to the creation of kaumātua health knowledge so that, firstly, the ageing population is seen to be valued and, secondly, the ageing population is given mana motuhake—the responsibility of taking on new and vital roles as their life situations evolve. As a result, the research objectives are informed by the position that transformative outcomes for kaumātua are symbiotically related to transformative outcomes for the broader Māori communities. These transformative outcomes have the potential to make lasting impacts for Māori communities. The ultimate goal is transformational change in the way kaumātua are recognised, supported, and served by the health system.

## Data Availability

The datasets used and/or analysed during the current study are available from the corresponding author on reasonable request.

## Glossary

HRQOL: Health-related quality of life
ICEA: Incremental cost effectiveness analysis
ICER: Incremental cost-effectiveness ratio
SRMR: Standardized root mean square residual
Aotearoa: New Zealand
Hauora: Health
Hapū: Subtribe
Hinengaro: Mind, thought, intellect
Iwi: Tribe
Kaupapa Māori: Research by Māori for Māori
Koha: Offering
Mana: Status and prestige
Mana motuhake: Autonomy, identity and self-actualisation
Māori: Indigenous people of New Zealand
Mātauranga: Indigenous knowledge
Pono: Truth, integrity
Te Ao Māori: Māori epistemology
Te Kupenga: Māori Social Survey
Teina: Peer education recipient
Tikanga: Customs and protocols
Tinana: Body
Tino rangatiratanga: Independence and autonomy
Tuakana: Peer educator
Tuakana-teina: Older sibling/younger sibling
Wairua: Spirit
Whakawhanaungatanga: Making social connections
Whānau: Extended family
Whanaungatanga: Social health
